**Downstream care pathways**				
	Number and proportion of referrals for the management of each IC deficit		This measures care coordination: (1) number of referrals made to services for management of each IC deficit and (2) proportion of referrals to each service with the denominator as the total number of referrals	Adoption Penetration Fidelity
	Number and proportion of actualized referrals for the management of each IC deficit		This measures care coordination: (1) number of actualized referrals to services for management of each IC deficit and (2) proportion of actualized referrals to each service with the denominator as the total number of referrals	Reach Penetration Costs
**Capability building**				
		Number of staff trained to conduct CFS and IC screening, and to provide referrals to follow-up assessments and care pathways Include breakdown by occupation (doctor, nurse, care coordinator, and patient service associate)	Capability building for screening and delivery of referrals	Adoption Feasibility Acceptability Costs

#### Study Sample and Data Source

The sample includes all recruited older adult participants. Each of the 5 clinics will collect and provide data to the research team. Table 3 summarizes the list of process indicators.

### Study Component 2: Fidelity Indicators for Implementation Strategies

#### Aim

We aim to assess the fidelity of the selected implementation strategies.

#### Study Procedure

We will monitor and track the fidelity of operationalizing each selected ERIC implementation strategy across the specified domains (actor, action, action target, dose, or temporality), using a comprehensive set of indicators [45]. In other words, we will assess whether each strategy is delivered in the feasibility study as originally intended during the co-development phase.

Indicators will be collaboratively designed by the research team and clinic implementation leads. Data will be collected regularly by clinic implementation leads and frontline implementers. The research team will systematically document any deviations from the planned implementation and discuss them with clinic implementation leads. Adaptations to strategies, if any, will also be documented. For example, in the case of the implementation strategy involved educational sessions for capability building on IC screening, we will assess whether the planned elements, such as the trainers (actor), attendees (target), and the frequency and duration of training (dose), are delivered as intended. If discrepancies arise, we will explore whether fidelity can be improved or whether adaptations are needed. In addition, we will focus on sustainability and scalability, such as whether the frequency and dose of the strategies are sustainable within the clinic and adaptable for scaling up to other clinics.

### Study Component 3: Qualitative Study

#### Aim

Broadly, we aim to qualitatively assess:

The level of feasibility (implementation, acceptability, adoptability, practicality, and adaptability), sustainability, and scalability of IMPACTFrail’s core components and implementation strategies, and barriers and facilitators to their attainment.Effectiveness of implementation strategies. This refers to the attribution of implementation strategies to attaining feasibility, sustainability, and scalability.

#### Study Sample and Data Source

Study participants will include older adult participants, clinic implementation leads who oversaw the planning and execution of IMPACTFrail, and frontline health care providers involved in the program’s core functions (doctors, nurses, care managers, care coordinators, allied health professionals, and support staff). We will conduct purposive sampling and sample sizes will be guided by the concept of sufficiency [51,52]. First, we will include older adults who participated in IMPACTFrail. We aim to interview a minimum of 3-4 older adults per clinic, with a total of at least 15 participants (approximately 10% of the targeted 36 recruited participants per clinic). We will sample the older adults using maximum variation for representation across demographic variables such as sex, ethnic groups, and age groups. Second, the qualitative study component will include clinic implementation leads who oversaw the planning and execution of IMPACTFrail and frontline health care providers involved in the program’s core functions (doctors, nurses, paraprofessional support staff). We anticipate only a small number of health care workers being involved in this small-scale pilot study. Hence, we will aim to sample all implementation leads at each clinic, estimated to range from 2 to 4 individuals per site. Additionally, we aim to sample frontline health care workers across every occupation who was involved across each central function of IMPACTFrail. Nurses and paraprofessional support staff in the qualitative study would need to have conducted IC screening for at least 5 older adults and doctors would need to conduct follow-up clinical assessments to assess intrinsic capacity deficits for at least 5 older adults. Interviews and focus groups with clinic implementation leads and frontline health care providers will be conducted in English, while interviews with older adults will be in either English or Chinese.

#### Study Procedure

As mentioned, both data collection and data analysis will be guided by the 4 feasibility criteria, the updated CFIR and its Outcomes addendum, TDF, and ERIC taxonomy [31,32,49]. We will expand CFIR’s Individual Characteristics domain by mapping determinants of capability, opportunity, and motivation to TDF domains [69,70]. The ERIC taxonomy informs the refinement of existing implementation strategies and selection of new strategies [32]. The semistructured topic guides elicit data that inform the 4 feasibility criteria, CFIR-based and TDF-based barriers and facilitators, and suggestions on new ERIC strategies. For example, for the criteria on implementation, we will obtain perspectives from implementers on the barriers and facilitators to delivering IMPACTFrail’s core components and implementation strategies (eg, mobilizing program champions, attending training), and perspectives on the extent that the strategies enabled the implementation of IMPACTFrail. Older adults will share about the barriers and facilitators of participating in IMPACTFrail and receiving implementation strategies (eg, patient educational materials) and the extent to which the strategies have facilitated their participation.

We aim to conduct 2 rounds of 14 interviews with clinic implementation leads across all 5 clinics. The first round of interviews will be conducted within the first 2 months of IMPACTFrail’s roll out. This will inform early implementation barriers to refine its delivery and inform additional support required. The second round of interviews will be conducted toward the last 4-5 months of the study and after the first 20-25 older adults have been recruited. This is to elicit their perspectives on how implementation has progressed, new barriers and facilitators that arose, and insights on improving the program. Additionally, we will conduct interviews or focus groups with frontline health care providers involved in delivering IMPACTFrail’s core functions. In the first instance, we will aim to conduct focus groups, as opposed to interviews, among the health care providers who worked as a team, if scheduling allows.

Deductive analysis will be guided by the frameworks and concurrent inductive analysis will reveal emergent barriers, facilitators, and themes. Two trained research team members will code verbatim transcripts independently and subsequently reconcile discrepancies. Framework analysis will be conducted [71]. This allows timely charting of data into a framework matrix, generation of themes by linking conceptually related codes, and directly addressing the feasibility criteria (Table 2). We will conduct a thematic analysis using data collected across all 3 regional health systems, as we anticipate cross-cutting barriers, facilitators and learning points across study sites. We will also identify contextual insights specific to each regional health system. This analytic approach allows us to synthesize cross-site patterns with a larger amount of data, while accounting for differences in organizational context, and directly address the feasibility of implementation across settings. A pragmatic approach of concurrent data collection and analysis will be adopted to ensure timely reporting of findings to clinic leadership and stakeholders to support the preparation of the scaled-up phase [72-75]. Microsoft Excel and NVivo 12 (QSR International) will be used for data management.

### Study Component 4: Cost Analysis

#### Aim

We aim to estimate the cost of developing and delivering the program and implementation strategies, with the purpose of informing the amount of resources required to sustain and to expand the program beyond the feasibility study.

#### Study Procedure and Data Source

First, we will compute developmental costs, which comprise (1) developing IMPACTFrail’s core functions, and (2) developing each implementation strategy. The expenditures on manpower (eg, health care providers involved in the co-development phase) and other expenses (materials, printing, etc) will be aggregated. Second, program costs will be derived from the costs of (1) delivering IMPACTFrail’s core components, and (2) operationalizing each implementation strategy. The expenditures on manpower, equipment, and operating expenses will be aggregated.

A time-driven, activity-based micro-costing approach will be used to estimate costs related to manpower resourcing [76,77]. Specifically, this will be derived from the unit cost multiplied by the intensity of use and duration of use. The unit cost will be estimated based on financial records or the standardized workforce unit cost for implementers obtained from the clinics. The intensity and duration of use will be derived from self-reported time spent for a select list of activities by implementers to deliver the program [78]. We will only use financial statements or costs self-reported by implementation leads to obtain unit costs on equipment and other operating expenses and their intensity of use.

Within each site, we will present the cost associated with (1) developing IMPACTFrail’s core functions, (2) developing each implementation strategy, (3) delivering IMPACTFrail’s core functions, (4) delivering each implementation strategy, (5) total developmental cost, (6) total program cost, and (7) total costs.

### Study Component 5: Program Description

We aim to produce written program descriptions across clinics guided by frameworks including the Template for Intervention Description and Replication (TIDieR) checklist or the Aims, Ingredients, Mechanism, and Delivery (AMID) framework [79,80]. The program descriptions will facilitate transparency and replicability.

### Study Component 6: Logic Model and Theory of Change

The logic model and theory of change depict a visual representation of the resources, key activities, outputs, outcomes, and plausible causal pathways connecting them [81,82]. Figure 2 displays the initial theory of change. During this feasibility study, we will refine the logic model and theory of change. This updated logic model and theory of change will guide our understanding on the mechanisms of change and on the short to longer term health outcomes to evaluate in the future study.

**Figure 2 figure2:**
[figure not shown]
Initial logic model and theory of change. Bold arrow represents the link of an activity to outputs or outcomes. Broken arrow represents the link of an activity to outputs or outcomes. ADL: activity of daily living; CFS: Clinical Frailty Scale; ED: emergency department; GERI: Geriatric Education & Research Institute; HR-QoL: health-related quality of life; iADL: instrumental activity of daily living; IC: intrinsic capacity; LOS: length of stay; SOC: specialist outpatient clinic; SOP: standard operating procedures;.

### Triangulation of Findings

For each of the 4 feasibility criteria, the findings across study components will be presented and narratively triangulated (Table 2). Next, findings across all criteria will be narratively triangulated and assessed holistically to inform feasibility and readiness to scale. Briefly, for instance, under the criteria on implementation, we will triangulate the quantitative process indicators on completion rates of IC screening, along with CFIR-based barriers to participating perceived by older adults and barriers to implementing IC screening by health care providers. Under the criteria on practicality, we may triangulate the cost analysis of incorporating IC screening into clinic workflows, such as manpower and operating costs, CFIR-based barriers on resource allocation and management, and perspectives on sustainability. Under the criteria on adaptability, we will elicit if the barriers could be mitigated by implementation strategies and refinements to the program. A key feasibility assessment result that will suggest a “go” is at least 80% of the targeted recruitment at each of the participating clinics; that is, at least 29 of the targeted 36 older adults are recruited into the study and complete IC screening. This will demonstrate that the key novel core function of the program, which is to deliver IC screening of 6 health domains, is feasible. Importantly, we will be guided and informed by the findings across the multiple study components and methodologies. Each of the 3 regional health systems in Singapore will be engaged. Overall, we will evaluate the readiness to scale IC screening to more older adults at the 5 clinics and to additional new clinics across the 3 health care systems. Stakeholders will be engaged to review the findings and discuss readiness to scale, including research directors from the 3 health care systems, health care administrators (clinic leadership), and frontline health care providers. This process is aligned with the UK MRC Framework, FAID, and implementation research frameworks.

### Ethical Considerations

Ethical approval for this study was obtained from the NHG Domain Specific Review Board (ECOS Ref: 2024-3878). Written informed consent will be taken from all participants prior to their participation in the study. Older adult participants will receive SGD $30 (US $23.65) upon completion of informed consent-taking and IC screening, and SGD $50 (US $39.42) upon completion of the interview. All data collected will be anonymized and securely stored in a restricted-access network accessible only to the research team.

## Results

The study was funded in September 2024. Data collection for the feasibility testing of IMPACTFrail commenced in April 2025 and will conclude by March 2026. As of manuscript submission, only 98 participants have been recruited across 5 sites. Recruitment, data collection, and data analysis are still ongoing. The results are expected to be published in early 2027.

## Discussion

### Principal Findings

IMPACTFrail seeks to translate Singapore’s National Frailty Strategy and the WHO ICOPE framework by serving as an IC detection and management program for mildly frail older adults in primary care [16]. It contributes to a holistic approach to healthy aging by enabling early mitigation of frailty progression and optimizing functional ability. At a broader level, it is aligned with the WHO public health framework on healthy aging [7], strengthens Singapore’s contribution to the United Nations Decade of Healthy Ageing (2021-2030) [83], and complements national initiatives on preventative care for chronic conditions in primary care (eg, Healthier SG) and aging well in the community (eg, Age Well SG) [41,42].

The implementation and evaluation of the ICOPE framework in real-world practice is still in its nascence [17]. A systematic review reported that most studies have only used IC primarily as an outcome measure, rather than to inform intervention design [84]. The existing studies have focused on examining the prevalence of IC deficits or tool performance [85-87]. Implementation of the ICOPE programs in the community by early adopters in France and China demonstrated general acceptance of IC screening, but there are still gaps in understanding how to increase uptake and adherence among less activated older adults, and scale up beyond the feasibility testing sites that had more resources and stakeholder buy-in [19-21]. In Korea, Won [38] described the first small-scale ICOPE program implemented in primary care, contextualized to concurrently assess frailty and IC, using a 53-item screening approach. However, scaling up and effectiveness have not been reported.

In response, our adoption of a systematic and staged approach grounded in implementation science aims to accelerate the translation of Singapore’s National Frailty Strategy and the WHO ICOPE framework with high reach, fidelity, adoption, sustainability, and scalability. Moreover, embedding implementation considerations from the outset may strengthen the program’s design and delivery, hence improving its effectiveness, sustainability, and scalability in real-world settings. If the findings indicate limited effectiveness, the likelihood of confounding from poor implementation and fidelity is lower; conversely, effectiveness elicited under research study conditions tends to be better sustained in real-world settings [88-90]. A second key strength is the integration of complex intervention research and implementation research frameworks to guide the co-development of the program and implementation strategies, the feasibility assessment, and the qualitative study. This integrated approach enhances methodological rigor and increases the likelihood of successful and contextualized implementation of a complex intervention. Third, IMPACTFrail is co-developed from the outset in collaboration with multiple stakeholders across all 3 regional health systems in Singapore. This is imperative in facilitating scalability across more clinics within each cluster and reduces cross-cluster fragmentation of services. Fourth, our feasibility assessment is informed by published guidelines on conducting feasibility studies, precise mapping of study components to feasibility criteria, and adopting a mixed methods approach. This facilitates the depth and quality of insights through triangulation of findings.

There are several potential limitations. First, variations in eligibility criteria across clinics may limit the comparability of findings across sites and reduce generalizability. However, this reflects the real-world implementation context of IMPACTFrail, which is operationalized across three public health care clusters with distinct workflows, resources, and different population needs. As such, contextual adaptations guided by complex intervention research and implementation science frameworks are necessary. While this may limit generalizability, it generates insights to inform the future scale-up of IMPACTFrail and other similar programs in primary care. Second, findings may be less generalizable to settings beyond primary care and to older adults who are not mildly frail. However, insights related to common barriers, such as capability building, resource allocation and patient-level behaviors, will be applicable. We will also report how these insights are used to refine the delivery of the program’s core steps and implementation strategies to support future scale-up. Importantly, this article still serves to disseminate generalizable knowledge on the implementation research methodologies and approaches to co-develop an ICOPE-based intervention with multiple stakeholders from the outset, and the structure use of feasibility testing prior to a larger main study. Third, the feasibility study does not include a comparator arm. However, the primary aim is not to assess effectiveness but to apply implementation science methodologies that enhance the likelihood of sustainability and scalability of a complex intervention nationwide. Effectiveness outcomes will be evaluated in a subsequent hybrid effectiveness-implementation study [57,58], which will be statistically powered to evaluate impacts on patient outcomes (eg, function, quality of life), health care use, and cost effectiveness. Lastly, tracking actualization rates of health and social care services for managing IC deficits may be incomplete due to the absence of a common information technology system across public primary care, private specialist clinics, and selected community organizations. Nevertheless, referral actualization within the primary care setting (eg, memory clinic and health and wellness clinic) and most public specialist outpatient clinics will be captured and monitored.

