#### Eligibility Criteria and Sample Size

Eligibility criteria include (1) registered patient of the clinic, (2) aged 60 years and older (3 of 5 clinics) or aged 65 years and older (2 of 5 clinics), (3) mildly frail, assigned by a trained health care provider as CFS score 4 or 5, and (4) able to provide informed consent independently or through a legally authorized representative. Exclusion criteria include (1) administered comprehensive geriatric assessment in the past 12 months or (2) at the time of this writing, being under the care of a geriatrician or patient of a geriatric specialist outpatient clinic.

Older adults who meet these eligibility criteria will be given information on the IMPACTFrail health care program and the research study verbally and via a hardcopy brochure by a paraprofessional care coordinator or nurse. A trained research assistant will obtain written informed consent from each older adult individually and address any queries from potential participants. Consent-taking to be recruited as a participant of the IMPACTFrail study will be conducted prior to intrinsic capacity screening. Recruitment will be conducted over approximately 9 months, continuing until each clinic reaches its target of 36 participants. All older adults will only need to go through this process once. Additionally, a subset of these older adult study participants of IMPACTFrail who participate in in-depth interviews of the qualitative study will undergo a separate informed consent process before their interviews. This informed consent-taking will be facilitated by trained researchers.

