**Follow-up assessment**				
		Number and proportion of referrals to follow-up assessment for each IC deficit	This measures care coordination: (1) number of referrals made to services for follow-up assessment for each IC deficit and (2) proportion of referrals to each service with the denominator as the total number of referrals	Reach Adoption Penetration Fidelity
		Number and proportion of actualized referrals to follow-up assessment for each IC deficit	This measures care coordination: (1) number of actualized referrals to services for follow-up assessment for each IC deficit and (2) proportion of actualized referrals to each service with the denominator as the total number of referrals	Reach Acceptability Costs

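### Table 3 counts management referrals whose attendance cannot be tracked in the denominator of the actualization proportion, so for the services affected the reported rate is only a lower bound

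*Protocol article*

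**What the plan says.** **Indicator.** In Table 3 of the protocol article, under Downstream care pathways, the actualization indicator for managing each IC deficit is a count and a "proportion of actualized referrals to each service with the denominator as the total number of referrals". The Follow-up assessment block uses the same construction, beginning with the "number of actualized referrals to services for follow-up assessment for each IC deficit".

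**Tracking.** The last limitation under Principal Findings in the Discussion says that "tracking actualization rates of health and social care services for managing IC deficits may be incomplete". The reason given is the "absence of a common information technology system across public primary care, private specialist clinics, and selected community organizations". The same paragraph adds that referrals within primary care and "most public specialist outpatient clinics will be captured and monitored".

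**Timing.** Eligibility Criteria and Sample Size states: "Recruitment will be conducted over approximately 9 months, continuing until each clinic reaches its target of 36 participants". According to the Results section, data collection "commenced in April 2025 and will conclude by March 2026". Table 3 times the screening steps but attaches no time window to referral or attendance.

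**Use.** The Aim of Study Component 1 says that the indicators show whether patients follow through along the whole care journey. Triangulation of Findings sets one numerical go threshold: at least 29 of 36 older adults per clinic recruited and IC-screened.

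**The concern.** The definition and the limitation do not fit together. The limitation says that for some services the study may not learn whether the patient attended. The definition nevertheless keeps every referral in the denominator, so an unknown outcome has the same effect on the proportion as a known non-attendance. The protocol discloses that tracking is incomplete, but it neither says that the resulting rate is a lower bound nor changes the indicator.

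This matters because the article already expects patients to have difficulty following through after screening (Hypothesis 2). A low rate caused by missing information could be read as confirming that expectation. Referral workflows are allowed to differ between clinics, so the untracked share may differ too. A clinic that refers more to private or community services would then look worse for reasons unrelated to feasibility.

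A second, smaller problem is unequal observation time. Participants recruited late have less time for a referral to be made and attended before data close.

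**Working it through.** The protocol states no actualization rate, expected rate or untracked share, so there is no plan figure to reproduce.

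**1. Denominator**

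Inputs: the denominator is all referrals (Table 3). Tracking is incomplete for some management services (Discussion). The untracked share *u* is not given, so values are assumed. A true rate of 70% is also assumed.

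If untracked referrals count as not actualized, then

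reported rate = true rate × (1 − *u*)

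| Assumed *u* | Reported rate when the true rate is 70% |
|---|---|
| 10% | 0.70 × 0.90 = 63% |
| 20% | 0.70 × 0.80 = 56% |
| 30% | 0.70 × 0.70 = 49% |
| 40% | 0.70 × 0.60 = 42% |

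A service with no tracking at all (*u* = 100%) reads 0% whatever its attendance.

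The same arithmetic under the proposed reporting, for 100 referrals with 70% of tracked referrals attended:

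| | 20 untracked | 40 untracked |
|---|---|---|
| Tracked and attended | 0.70 × 80 = 56 | 0.70 × 60 = 42 |
| Table 3 as written | 56/100 = 56% | 42/100 = 42% |
| Observable denominator | 56/80 = 70% | 42/60 = 70% |
| Bound, no untracked attended | 56/100 = 56% | 42/100 = 42% |
| Bound, all untracked attended | (56 + 20)/100 = 76% | (42 + 40)/100 = 82% |

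The figure in Table 3 equals the lower bound. The observable denominator recovers 70% for all referrals only if tracked and untracked services have the same true rate, which is why the bounds are needed as well.

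**2. Observation time (secondary)**

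April 2025 to March 2026 is 12 months. With about 9 months of recruitment, the first participant is observed for about 12 months from enrolment and the last for about 12 − 9 = 3. The time per referral is shorter, because a referral comes after screening.

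The effect depends on waiting times, which the protocol does not give. Assume exponential waits with median *m*, referral at enrolment, and even recruitment, so that observation is uniform from *a* to *b* months. The share of eventual attendances seen by data close is the mean of 1 − exp(−ln 2 × *t*/*m*) over that range. Compare a clinic recruiting over 9 months (observation 3 to 12) with one that reaches its target in an assumed 4 months (8 to 12):

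| Median wait | 9-month recruitment | 4-month recruitment |
|---|---|---|
| 1 month | 98% | 100% |
| 3 months | 79% | 90% |
| 6 months | 56% | 68% |

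These are shares of eventual attendances. With an eventual rate of 70% and a 3-month median, the observed rates are 0.70 × 0.790 = 55% and 0.70 × 0.897 = 63%. With short waits the effect nearly vanishes.

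**The case against.** The strongest reply has four parts.

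- **The limitation is disclosed, and the article does not say how unknown status is coded.** Coding may sit in the full protocol or SAP. This stands in part: that untracked referrals count as not actualized is the literal reading of Table 3, not an explicit statement. But the denominator is written down here, and disclosing the gap does not change it.
- **The proportion is given for each service, so an untracked service mainly distorts its own row.** This stands. Rows for primary care and for captured public specialist clinics are not diluted. The 56% and 42% apply to a service with that untracked share, or to a deficit or clinic total that mixes services. The wording could also mean the total over all services. A per-service figure would then not be an actualization rate at all, which should be clarified at the same time.
- **The consequences are limited.** This stands too. A reader might infer that the go decision is affected, but the 29-of-36 threshold uses only recruitment and completed screening. A reader might also take actualized referrals to be the only quantitative evidence on management. Table 3 also counts management referrals made, and the cost analysis covers delivery of the core functions.
- **The gap does not reach every actualization rate.** The limitation concerns services for managing deficits. For follow-up assessment within primary care attendance is captured, so mainly the timing point remains.

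On timing, a reader might infer large differences by contrasting a clinic that recruits only in the first half of the period with one that recruits only in the second. The protocol describes no such pattern, and the size rests on assumed waits.

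**Conclusion.** The concern holds for management referrals. As defined, the proportion is a lower bound for services whose attendance is not fully visible, and for any deficit or clinic total that includes them. It is low by a factor of one minus the untracked share. The direction follows from Table 3 and the Discussion, provided that unknown outcomes are left out of the numerator. The size cannot be determined from the documents, and the percentages above are illustrations.

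The effect falls on descriptive reporting, the comparison of sites and the triangulation, not on the go threshold. Unequal observation of about 3 to 12 months follows from the stated calendar, but its importance depends on unknown waits, so it is secondary. The change is worth making before analysis.

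**What to change.** 1. In Table 3, Downstream care pathways, define the denominator as referrals to services whose attendance the study can observe, and list those services for each clinic. State whether the denominator is per service or over all services.
2. Report the number of untracked referrals separately, by service and clinic.
3. For all referrals, give two bounds: no untracked referral attended, and all attended.
4. Where referral and attendance dates are available, also report the proportion actualized within one common time from referral, among referrals with at least that much observation. Do this before comparing clinics. With 36 participants per clinic, a simple proportion suffices; time-to-event curves by service would rest on very small cells.

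The cost is a smaller denominator and one or two extra table columns. Items 1 to 3 need only a record of which services can be tracked. Item 4 needs dates, and the article does not say whether these are collected, so it is conditional.
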